## Abstract

**Introduction::**

CRC, the incidence of the fourth highest among males and the third among females, is one of the malignant tumors that seriously threaten human health. The principle of treatment for advanced stage CRC is a multidisciplinary and comprehensive treatment based on chemotherapy, which always bring significant toxic side effects. CHM has advantages in the treatment of tumors with the effect on improving clinical symptoms and reducing side effects. GGQL formula is mainly used for treating abnormal defecates caused by damp-heat, so we will evaluate the clinical efficacy and safety of modified GGQL formula for patients with advanced CRC with the type of damp-heat in this study.

**Methods::**

Multicenter RCT with two parallel groups in three hospitals planning to recruit 120 CRC patients with the type of damp-heat will be conducted. The control group will be treated by basic antitumor therapy and the treatment group will use modified GGQL formula plus basic antitumor therapy. The primary outcomes will be quality of life, TCM symptom score, PFS and OS, and the secondary outcomes will be performance status, size of tumor, tumor marker in the serum, tumor microenvironment and immune status. All analyses will be based on an intention-to-treat principle. This study was approved by the Human Research Ethics Committee of Shanxi Province Hospital of Traditional Chinese medicine (2021Y-06017). The results will be published in relevant journal.

**Discussion::**

The results of this RCT will contribute to Chinese herbal medicine for treating CRC patients with the type of damp heat accumulation.

**Trial registration::**

ChiCTR2100050754 (September 4, 2021).

## Introduction

1

Colorectal cancer (CRC) is one of the malignant tumors that seriously threaten human health. According to the 2020 global epidemiological statistics on cancer published by the International Agency for Research on Cancer (IARC) of the World Health Organization, CRC has the second highest mortality rate and the third highest incidence rate of all malignancies with 935,200 deaths and 1,931,600 new cases worldwide. In China, there were about 560,000 new cases of CRC in 2020.^[1]^ The incidence of CRC is the fourth highest among males and the third among females.^[2]^

Patients with CRC have no obvious symptoms in the early stage, only atypical symptoms such as abdominal discomfort, fecal occult blood or indigestion, which are not easy to attract patients’ attention. Once CRC diagnosed, 20% to 30% of patients are already in advanced stage, losing the chance of surgery.^[3]^ The 5-year survival rate for advanced CRC is <10%.^[4]^

Currently, the principle of treatment for early stage CRC is a multidisciplinary and comprehensive treatment based on surgery. While 50% of patients with CRC may have recurrence or metastasis within two years after radical surgery, of which 20% to 30% have local recurrence and 50% to 80% have distant metastasis.^[5]^

For patients who cannot be resected, chemotherapy is recommended.^[6]^ However, chemotherapy drugs often show significant toxic side effects, such as reduction of autoimmunity, inhibition of bone marrow hematopoiesis and gastrointestinal reactions. Therefore, therapies which can increase efficacy and reduce side effects of chemotherapy need to be developed.

Chinese herbal medicine (CHM) has advantages in the treatment of tumors, with the effect on improving clinical symptoms, enhancing patients’ immunity and quality of life, reducing the adverse effects of radiotherapy and chemotherapy, and prolonging survival through the coordinated effects of multiple components, targets and pathways in the process of tumor occurrence and development.^[7]^

In traditional Chinese medicine (TCM) theory, the common pathological factors for CRC are dampness, heat, stasis and deficiency, and dampness and heat can be mutually embedded in the intestine, and some studies have shown that dampness and heat can promote liver metastasis and the mechanism of occurrence may be related to the upregulation of VEGF, MMP-2 and MMP-9 expression.^[8–10]^ Damp-heat is one of the most common types of colorectal cancer. It accounts for about 30% of the overall identification of colorectal cancer.^[11]^

Gegen Qinlian (GGQL) formula is mainly used for treating abnormal defecates caused by damp-heat. Modern medical research has proved that GGQL formula has pharmacological effects such as antipyretic, anti-inflammatory, antibacterial, antiviral antispasmodic inhibiting gastrointestinal motility and enhancing the immunity of the body, and is widely used in the treatment of clinical diseases such as bacillary dysentery, intestinal typhoid, acute and chronic gastroenteritis, and infantile diarrhea.^[12]^ Modified GGQL formula is based on GGQL formula with the addition of Muxiang), Chunpi and Dongguaren, which is clinically effective in patients with intermediate to advanced CRC.

## Objective

2

In this study, we will evaluate the clinical efficacy and safety of modified GGQL formula for patients with advanced CRC with the type of damp-heat. We will also aim to investigate the relationship between modified GGQL formula and life quality of CRC patients and cellular immunity.

## Methods/design

3

### Trial design

3.1

This multi-centers, randomized controlled clinical trial with parallel groups of 120 CRC patients with the type of damp-heat will be conducted according to the flow diagram and will last for 2 years, scheduled to start in October 2021 (Fig. 1).

**Figure 1 F1:**
[figure not shown]
Study flowchart.

### Location and setting

3.2

All assessments will be conducted at Shanxi Province Hospital of Traditional Chinese medicine, Shanxi Province Hospital of Oncology, and the Affiliated Hospital of Shanxi University of Chinese Medicine within the department of oncology, Taiyuan, Shanxi, China. And this study was approved by the Human Research Ethics Committee of Shanxi Province Hospital of Traditional Chinese medicine (2021Y-06017).

### Participants

3.3

#### Eligibility criteria

3.3.1

The patients are planned to be recruited from the hospitals mentioned above, and the inclusion criteria would be verified.

The inclusion criteria for this RCT are following:

1.Age > 18 years and the excepted survival ≥3 months;2.Patients with colorectal cancer who have been diagnosed pathologically or cytologically according to the above-mentioned western diagnostic criteria and TCM syndrome type diagnostic criteria;3.Patients with TNM stage IV, postoperative recurrence, metastasis or loss of operation without operation, did not take Traditional Chinese medicine in recent 1 month;4.No other primary tumors and serious heart, liver, and kidney diseases;5.Those who have the telephone number and address of follow-up, and are willing to cooperate with follow-up, have relatively complete medical records, and have signed informed consent.

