### Procedures (Template)

3.4

CRC patients will be evaluated by an oncologist, and after the initial evaluation, the patient with indication on using modified GGQL formula and fit the eligibility criteria of this RCT will be referred for specific evaluation by an oncologist with at least 3-year experience in the evaluation and prescription of modified GGQL formula. All the included participants would sign terms of free and informed consent.

The participants fitting the criteria of inclusion will be randomized to be divided into two groups: the treatment group (using modified GGQL formula plus basic antitumor therapy) and the control group (basic antitumor therapy).

The first evaluation should occur before treatment and then the participants will accept 12 weeks treatment in the treatment group or the control group. And they will be evaluated each three weeks after interventions.

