### Randomization and blinding

3.5

The process of randomization will be carried out by stratified block randomization method with the block size setting as four and six, and the center was taken as the stratified factor. The participants will be divided into the treatment group and the control group randomly with a ratio of 1:1. We will use the ‘Proc plan’ of SAS9.3 statistical analysis software for generating the random scheme. The central randomization system for clinical research (provided by the Oncology Department of Shanxi Hospital of Traditional Chinese Medicine) will be used for randomization. When qualified patients are enrolled, the randomization personnel or clinical investigators in each center will log into the central randomization system through telephone or Internet to apply for the randomization number.

Because of no herbal medicine used in the control group, it will hardly to blind the doctors and patients involved in this RCT.

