### Sample size calculation

3.10

The number of participants is capable to detecting according to the results of the previous study (1-year survival rate was 80% and the median overall survival was 25 months in the treatment group; 75% and 22 months respectively in the control group) with an alpha error of 0.05 and beta error of 0.2. Considering the 20% drop-out rates, the sample will be composed of 120 participants randomized into two groups.

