### Baseline assessments

3.11

Sociodemographic data are planned to be collected from the included patients, and also the data on duration of disease and previous herbal medicine treatments.

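### Line of therapy is left open at entry and appears in neither the stratification, the listed baseline data nor the OS/PFS analysis, which costs precision and interpretability

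*Protocol article*

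**What the plan says.** All references are to the protocol article.

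- **Entry (3.3.1, 3.3.2).** Disease status is set by "Patients with TNM stage IV, postoperative recurrence, metastasis or loss of operation without operation", prognosis by "Age > 18 years and the excepted survival ≥3 months". The one restriction on earlier treatment is herbal: "did not take Traditional Chinese medicine in recent 1 month". The exclusion list adds nothing on earlier chemotherapy.
- **Background treatment (3.6).** Three chemotherapy regimens are allowed. None is tied to a line.
- **Randomisation (3.5).** Allocation is 1:1 in blocks, and "the center was taken as the stratified factor". No other factor is named.
- **Baseline (3.11).** Besides sociodemographic data, the section lists "also the data on duration of disease and previous herbal medicine treatments". Line and prior chemotherapy are not listed.
- **Analysis (3.12).** OS and PFS are compared by Kaplan-Meier curves and a log-rank test with no stratum or covariate named. The subgroup factors are age, sex, tumour side, gene status and microsatellite status.
- **Planning (3.10).** The figures come from a previous study: "1-year survival rate was 80% and the median overall survival was 25 months in the treatment group", against 75% and 22 months in the control group.

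**The concern.** OS and PFS are two of the four primary outcomes in 3.7. As 3.3.1 is written, a patient starting a first regimen and a patient who has progressed on earlier regimens can both enter. If survival differs strongly between them, line is a prognostic factor of the kind one would normally balance or adjust for. The plan names centre for randomisation and five other factors for survival subgroups, but not line.

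Two things are at stake. With about 60 patients per arm, the arms may differ by chance in their later-line share, and an unadjusted comparison carries that difference into the estimate. The planning medians in 3.10 can also be applied to this trial only if the earlier study had a similar mix of lines, and the article does not say whether it did.

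**Working it through.** **Inputs from the protocol article:** 120 patients, 1:1, so 60 per arm; median OS 22 and 25 months (3.10). **Assumed, because the article gives neither:** a later-line share p of 20-50%; median OS of 22 months first-line and 10-14 months later-line; exponential survival within line; 24 months' follow-up.

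**1. Planned effect.** Under exponential survival the ratio is 22/25 = 0.88, and ln(0.88) = -0.128. This is the yardstick below. (The sample size of 120 does not follow from it: Schoenfeld's formula asks for 1,922 deaths at two-sided 5% and 80% power. That is a separate matter.)

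**2. Chance imbalance in later-line share.** SD of the between-arm difference = sqrt(2p(1-p)/60). Normal approximation for a difference of 10 points or more in either direction:

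| p | SD | 0.10/SD | Chance |
|---|---|---|---|
| 20% | 0.073 | 1.37 | 17% |
| 30% | 0.084 | 1.20 | 23% |
| 50% | 0.091 | 1.10 | 27% |

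Counting patients exactly (a difference of six or more between two binomials of 60) gives 21%, 27% and 32%, so the approximation is slightly low.

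**3. Effect of a 10-point imbalance with no drug effect.** Take 55% first-line in one arm and 45% in the other. For each line the hazard is ln2/median, and the arm's rate is expected deaths divided by expected person-months over 24 months.

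| Later-line median | Rate, 55% first-line | Rate, 45% first-line | Ratio | Share of planned log HR |
|---|---|---|---|---|
| 10 months | 0.0452 | 0.0489 | 0.925 | 0.078/0.128 = 61% |
| 12 months | 0.0417 | 0.0442 | 0.942 | 0.060/0.128 = 47% |
| 14 months | 0.0388 | 0.0406 | 0.956 | 0.045/0.128 = 35% |

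If the imbalance runs the other way, the ratios are the reciprocals, about 1.05-1.08.

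**4. Compared with ordinary sampling error.** The SE of a log HR is about 2/sqrt(deaths). It is 0.20 with 96 deaths (all patients left after 20% drop-out). It is 0.34 with about 34 deaths, the number expected if accrual is uniform over 24 months and the analysis falls at 24 months. Shifts of 0.045-0.078 are well below both.

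**5. Type I error.** In a simulated unstratified log-rank test with no drug effect, 60 per arm and medians of 25 and 10 months, rejection was 5.5% with a 30% later-line share and 5.4% with 50% (10,000 runs each). That is close to nominal.

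**6. Mixture median.** With medians of 22 and 10-14 months, a 30% later-line share gives an overall median of 17.1-19.1 months, and a 50% share 14.5-17.4. The 22-month control figure therefore depends on the mix of lines.

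**The case against.** The strongest reply is that broad entry with stratification by centre alone is an accepted pragmatic design. Randomisation already allows for chance imbalance, and steps 4 and 5 support this: the test level holds, and ordinary sampling error exceeds the line effect. That stands, and it limits the point to precision and interpretation. It can also be said that covariates belong in an analysis plan that is not shown. But 3.12 does fix the test and names the subgroup factors, and line is not among them.

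Several stronger readings are tempting, and the article does not support them:

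- *Line is not collected, so imbalance could never be seen.* Section 3.11 is one condensed sentence. It also omits tumour side, gene status and microsatellite status, which 3.12 uses, and 3.3.1 asks for reasonably complete medical records. One can say only that line is not listed.
- *Patients may enter in mid-course of chemotherapy.* Section 3.4 says "The first evaluation should occur before treatment and then the participants will accept 12 weeks treatment in the treatment group or the control group". It is not explicit that this means before chemotherapy, but it does not say the opposite.
- *The 3-month floor contradicts a 22-25 month median.* A minimum is compatible with a much higher median. Nor can early deaths before week 12 be predicted from the floor, since the share of patients near it is unknown.
- *The planning medians conflict with the Introduction's five-year survival below 10%.* That conflict appears only under exponential survival, which the figures in 3.10 do not follow: a 22-month exponential median gives 69% at one year, not 75%. A Weibull curve through 75% at 12 months and 50% at 22 months gives about 5% at five years; through 80% and 25 months, about 7%. Both agree with the Introduction.
- *The planning figures describe a different population.* The previous study's entry criteria are not shown. It may have had the same mix.

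**Conclusion.** The point holds as a matter of precision and interpretability. No line criterion is stated at entry, and line appears in none of the stratification, the listed baseline items, the survival test or the subgroups. Under the stated assumptions, a 10-point imbalance has roughly a one-in-six to one-in-four chance and would account for 35-61% of the planned log hazard ratio. It looks large mainly because the planned effect is small for 120 patients.

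A reader might infer that imbalance in line could mimic or hide the whole planned effect. That depends on the assumed share and medians. Over a wider set (first-line medians of 22 or 25 months, later-line 6 to 15, shares 20-50%), the chance that imbalance alone gives a 25:22 ratio of medians in either direction runs from about 0% to 32%. The article supplies nothing to choose within that range. There is no systematic bias and no inflated type I error.

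**What to change.** 1. Record line of therapy (first or later) and prior systemic treatment before randomisation, and list both in 3.11.
2. In 3.12, replace the plain log-rank test for OS and PFS with a log-rank test stratified by line, or a Cox model with line as a covariate. Fix the choice before outcomes are compared by arm.
3. In 3.10, say whether the study behind the 22- and 25-month medians admitted the same lines. If it did not, say so.

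The cost is one or two case-record fields taken from the medical record, and one model term. The gain is modest: about 1-4 points of power at hazard ratios of 0.5-0.6 under the assumed medians of 22 against 10-14 months, and an estimate that can be read with line accounted for. Adjustment afterwards is possible only if line was captured. Restricting entry to one line is not asked for; that would be a trade-off against recruitment and breadth, and this point does not depend on it.

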#### Exclusion criteria

3.3.2

1.Non-primary colorectal cancer with unclear diagnosis;2.Unable or unwilling to receive TCM treatment;3.The patient has developed intestinal obstruction, cannot take medication, needs intravenous high-energy nutrition, or has malabsorption syndrome or other diseases affecting gastrointestinal absorption, or has active peptic ulcer disease.

#### Discontinuing criteria

3.3.3

Any patients who are unwilling to use modified GGQL formula with or without reasons will quit this study.

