### Intervention

3.6

After specific evaluation by an oncologist, the participant will be divided into one of the two groups according to the randomization.

The treatment group: basic anti-tumor therapy combined with modified GGQL formula.

Basic anti-tumor therapies include:

1.mFOLFOX6 (Oxaliplatin 85 mg/m^2^ d1 + Leucovorin 400 mg/m^2^ d1 + Fluorouracil 400 mg/m^2^ d1 + Fluorouracil 2-2.4 g/m^2^ 46 h), the treatment period is 14 days; or2.FOLFIRI (Irinotecan + Leucovorin 400 mg/m^2^ d1 + Fluorouracil 400 mg/m^2^ d1 + Fluorouracil 2–2.4 g/m^2^ 46 h), the treatment period is 14 days; or3.XELOX (Oxaliplatin 85 mg/m^2^ d1 + Capecitabine 850–1000 mg/m^2^ bid d1-14), the treatment period is 21 days.

Modified GGQL formula is mixing and powdering by *Gegen*, *Huangqin*, *Huanglian*, *Muxiang*, *Chunpi*, *Donggua’er*, and *Paojiang*, which offered by Preparation Center of Shanxi Province Hospital of Traditional Chinese Medicine. The patients are planned to be used modified GGQL formula for 12 weeks.

The control group: basic anti-tumor therapy (the same as above).

All patients will be supervised by an experienced oncologist during this study.

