### Statistical analysis

3.12

The analysis will follow the principle of intention to treat (ITT). All statistical tests were conducted by two-sided tests and P values less than 0.05 were considered statistically significant. The description of quantitative indicators will calculate the number of cases, mean, standard deviation, median, minimum and maximum. Classification indicators are described by the number of cases and percentages of each category. For quantitative data, a mixed effect model was used to compare the change values of the two groups before and after treatment. The baseline score was taken as a covariable, and the grouping and central effect were considered in this analysis model. The dependent variable is the base change value of comparison point at each time point after treatment. Based on this model, the least square mean (LSMEAN) and the 95% confidence interval of the two groups will be calculated respectively. Kaplan–Meier method will be used to draw OS and PFS survival curves, and log-rank will be used to test the differences between the two groups. The differences of OS and PFS will be discussed in subgroup analysis according to age, sex, left and right colon, gene status, and microsatellite status.

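### Section 3.3.3 makes stopping the formula the same as leaving the study; this can happen only in the treatment arm and conflicts with the stated intention-to-treat analysis

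*Protocol article*

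**What the plan says.** The whole of section 3.3.3 (Discontinuing criteria) is one sentence: "Any patients who are unwilling to use modified GGQL formula with or without reasons will quit this study". What the patient leaves is the study, not only the formula.

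The other relevant statements in the protocol article are:

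- Section 3.3.2 already excludes, before enrolment, patients who are "Unable or unwilling to receive TCM treatment".
- Section 3.6 gives the formula to one arm: "The treatment group: basic anti-tumor therapy combined with modified GGQL formula". The control arm receives the basic therapy alone.
- Section 3.5 confirms that there is no herbal comparator and no blinding: "Because of no herbal medicine used in the control group, it will hardly to blind the doctors and patients involved in this RCT".
- On duration, section 3.6 says: "The patients are planned to be used modified GGQL formula for 12 weeks".
- Section 3.7 names four primary outcomes: SF-36 and TCM symptom score at baseline, week 6 and week 12, and PFS and OS by follow-up.
- On analysis, the abstract says: "All analyses will be based on an intention-to-treat principle". Section 3.12 repeats the principle.

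Nothing in the article says that a patient who stops the formula is still followed, or how that patient is analysed.

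**The concern.** Intention to treat compares all randomised patients, in the arm to which they were allocated, whatever they went on to take. It therefore needs outcomes from patients who stop the study treatment. A rule that turns stopping the formula into leaving the study cuts off those outcomes.

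A control patient has no formula to decline, so the losses from this rule fall on the treatment arm alone. The two arms then no longer differ by randomisation only. If those who stop differ in prognosis from those who continue, all four primary outcomes can be biased. OS and PFS are the most exposed, because they need data from well beyond the 12 weeks of formula. Outcomes that were never collected cannot be recovered at the analysis.

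**Working it through.** **Step 1: when the rule applies.** Unwillingness to receive TCM is already an exclusion criterion (3.3.2). If 3.3.3 were a second screen before randomisation it would add nothing. It stands under its own heading on discontinuation, so it applies to enrolled patients.

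**Step 2: to whom it applies.** Its wording covers any patient, but only the treatment group is given the formula (3.6) and the control group gets no herbal medicine (3.5). There is no matching rule for control patients.

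**Step 3: what it does to the analysis.** If follow-up ends at quitting, OS and PFS are censored there, and later SF-36 and TCM scores are missing. The log-rank test in 3.12 is then unbiased only if censoring is unrelated to prognosis. The mixed model in 3.12 is unbiased only if the missing scores can be predicted from the observed ones. Neither can be checked from the data.

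**Step 4: possible size.** The article gives no figure for stopping the formula, so there is none to reproduce. The following is an illustration for OS with no true effect.

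Inputs from the article: control median OS 22 months (3.10), and recruitment over 24 months (4.1).

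Assumptions: exponential survival; 12 further months of follow-up after accrual; a share q of each arm made up of patients who would quit if given the formula; quitters' hazard h times that of the other patients; quitting uniform over 0 to 3 months; censoring at quitting in the treatment arm only.

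The average hazard is ln2/22 = 0.0315 per month. The hazard of the other patients is 0.0315/(q·h + 1 − q). For q = 0.20 and h = 2 this is 0.0315/1.2 = 0.0263, and quitters have 0.0525.

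Apparent OS hazard ratio, treatment versus control, from a large simulation:

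| Share quitting | h = 0.75 | h = 1 | h = 1.5 | h = 2 | h = 3 |
|---|---|---|---|---|---|
| 10% | 1.03 | 1.00 | 0.97 | 0.94 | 0.91 |
| 20% | 1.05 | 1.00 | 0.92 | 0.88 | 0.81 |

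Setting the overall median at exactly 22 months, instead of the average hazard at ln2/22, moves the entries by about 0.01 at most.

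**Step 5: check by hand.** Take q = 0.20 and h = 2, and remove quitters entirely. With x the survival of the other patients at 22 months, an overall median of 22 months requires 0.2x² + 0.8x = 0.5. Then x = (−0.8 + √1.04)/0.4 = 0.5495. The hazard of the others is −ln(0.5495)/22 = 0.0272, and their median is 0.693/0.0272 = 25.5 months. The ratio 22/25.5 is 0.86. The simulated 0.88 is slightly closer to 1, as expected, because quitters contribute some time and events before they leave.

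**The case against.** The strongest reply is that 3.3.3 never says that data collection ends, that quitters are censored or that they leave the analysis. A trial can have withdrawals and still analyse everyone as randomised. Inclusion criterion 5 requires contact details and willingness to cooperate with follow-up, so survival could be ascertained. The exclusion of patients unwilling to receive TCM should keep the quitting group small. The handling of missing data commonly sits in a full protocol or SAP that is not shown.

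Part of this stands. A reader might infer that the rule makes intention to treat impossible. The article does not support that: quitters could nominally be kept in their arm by censoring or imputation. But being contactable does not override a rule that the patient leaves the study, and no SAP can analyse outcomes that were not collected. The point rests on a stated rule, not on missing detail.

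Three further inferences go too far:

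- **That the bias must favour the formula.** The rule applies with or without a reason. Section 3.9 lists nausea, vomiting and anorexia among the adverse events to be recorded, so poor tolerance or decline is a plausible reason to stop. Well patients may also stop, and the bias then reverses.
- **That 20% is the expected rate of refusal.** The 20% in 3.10 is an overall drop-out allowance for the 120 patients. Placing all of it on formula refusal in one arm is an upper illustration.
- **That the artefact exceeds the planned effect.** The article states no hazard ratio. Its medians imply 22/25 = 0.88, but its 1-year rates imply ln(0.80)/ln(0.75) = 0.78, which no entry in the table reaches. Lower values, about 0.70 to 0.73, arise only if quitters have 3 times the hazard of the whole-arm average. At 20% quitting the others then have (1 − 0.2 × 3)/0.8 = 0.5 times the average, so quitters have 6 times their hazard.

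**Conclusion.** Section 3.3.3 is wrong as written. It creates a loss of follow-up that can arise only in the treatment arm, and this conflicts with the intention-to-treat commitment in the abstract and section 3.12. That conclusion comes from the text alone and needs no assumed figure.

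The size and direction of any bias are not known. Under the assumptions above, with 10% to 20% quitting, the apparent OS hazard ratio runs from about 0.97 to 0.81 if quitters have 1.5 to 3 times the hazard of the other patients. It is 1.00 at equal hazard and about 1.03 to 1.05 at 0.75 times. The quitter share, the quitter hazards, the timing and the 12 months of added follow-up are assumptions. The illustration covers OS only; for PFS, SF-36 and TCM score the mechanism is the same but was not quantified.

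**What to change.** Reword 3.3.3 so that stopping the formula is separate from leaving the study, and reconcile it with 3.12. The text should say that:

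- patients who stop the formula keep the week-6 and week-12 assessments and the PFS and OS follow-up;
- they are analysed in the arm to which they were randomised;
- only withdrawal of consent to follow-up ends data collection;
- the date of stopping, and the reason if given, are recorded, so that the pattern of stopping can be described.

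This changes data collection only. It does not alter who stops the formula, or when.

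The cost is a short change to the protocol, a matching line in the consent text, and continued follow-up contacts for patients who stop. Those visits and calls are already planned for them as participants. Some patients will still withdraw consent to follow-up, but that loss can occur in either arm and is no longer created by the protocol in one of them.
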